### Interventions

The PAXonline Program for Panic Disorder is a 12-week internet-based treatment, which consists of cognitive-behavioral therapy modules, delivered with or without assistance from a therapist. The Panic Disorder Program contains 16 modules which address important cognitive behavioral psychotherapy elements such as: psychoeducation on the disorder and means of intervention; techniques for decreasing neurophysiological hyperarousal; cognitive restructuring; exposure to feared somatic sensations, alongside with situational (in vivo) exposures to reduce agoraphobic avoidance; positive emotions training; problem-solving training; behavioral activation and cognitive restructuring exercises to reduce symptoms of depression; relapse prevention. The treatment modules and the manual used to guide the intervention in our RCT were written based on empirically validated cognitive-behavioral models of anxiety disorders [74–76]. Each module can be completed in 15–40 min and the participants are provided with a recommended timetable (one or two modules per week, depending on the complexity of the content and the homework assignments). For a more detailed description of the intervention modules please refer to Table 3.

**Table 3 Tab3:** Paxonline panic disorder treatment

Modules	Short description
Introductory module. *Anxiety, from normality to pathology*	Psychoeducation concerning fear, anxiety, fight or flight response, the brain circuits involved in the fear response, etiology of anxiety and treatment directions. Normalizes patients’ reactions and sets correct expectancies.
Module 1. *Understand what’s happening with you*	Introductory information on panic attacks, panic symptoms and how panic disorder develops. Study cases and video illustrations. Patients begin to register PD related behaviors and thoughts using online worksheets.
Module 2. *Understand what you have to do*	Introducing treatment strategies, the treatment plan and boosting confidence and motivation for change.
Module 3. *Reduce hyperactivation through breathing retraining*	Information on the effects of hyperventilation, breathing regulation and abdominal breathing exercises.
Modules 4 and 5. *Reduce hyperactivation through autogenic training*	Inducing relaxation by using autogenic training exercises. Videos and audio files are provided for practice.
Module 6. *Reduce hyperactivation through physical exercises*	Psychological and biological benefits of physical exercises are presented; how to use them regularly.
Module 7. *Optimizing attentional functioning*	Attention biases in anxiety and panic disorder. Retraining attention away from the body and panic-like thoughts.
Module 8. *Changing maladaptive conscious cognitions*	The importance of catastrophic thoughts and attitudes. ICAR technique for cognitive restructuring:
	Identify catastrophic cognitions
	Challenge each dysfunctional cognition
	Find the Alternative cognition
	Repeat the procedure
Module 9. *Changing maladaptive unconscious cognitions*	Cognitive restructuring techniques for unconscious beliefs. Identify personal values and live by them.
Module 10. *Avoidance reduction through interoceptive exposure*	Explain the mechanism of avoidance and prepare for exposure exercises. Reduce fear of bodily sensations through interoceptive exposure.
Module 11. *Avoidance reduction through exteroceptive exposure*	Reduce avoidance behaviors through gradual exposure to feared situations.
Module 13. *Positive emotions development*	Increase positive emotions in daily life through cognitive and behavioral exercises drawn from positive psychology practices.
Module 14. *Relapse prevention*	Resume the intervention strategies, set the correct expectancies and make a plan to continue improvement and deal with relapse situations.
Module 12. *You learn how to solve problems (optional)*	Learn to organize problems according to importance and urgency. Implement problem-solving technique.
Module 15. *Reducing depressive symptoms associated with panic – behavioral activation (optional)*	Depression symptoms co-morbid to panic disorder. Behavioral activation techniques.
Module 16. *Reducing depressive symptoms associated with panic – cognitive restructuring (optional)*	ICAR technique for cognitive restructuring of dysfunctional cognitions that induce and maintain depression.

#### Guidance

Both treatment groups use the same intervention, but the first group also receives guidance from a licensed psychotherapist. The participants in this group have regular 15–30 min Skype sessions (the length depends on the complexity of the modules and the needs of each patient) with their psychotherapist. The first Skype session is introductory and takes place in the first week of the treatment, after the participant completed the module “Anxiety, from normality to pathology”. From then on, a new session is scheduled almost every week, but only after the participant has completed the corresponding modules from the recommended timetable. The sessions are scheduled via an encrypted asynchronous communication system available on the treatment platform. The participants can also use this system between two Skype sessions if they need further clarifications from their therapist.

In total, there are 10 Skype sessions programmed. During these sessions, held over secured Skype, the psychotherapist checks if the participant has completed and understood each module, answers questions, and helps the participant carry out the recommended exercises. The main purpose of each online session is to make sure that the patient has everything he needs in order to put the recommended exercises into practice regularly. That means, according to a behavioral model of change [84], the psychotherapist try to set the necessary antecedents by providing procedural knowledge (‘I know what I have to do and how to do it”), self-efficacy (“I believe I can do it”) and motivation (“I’m convinced that it is worth doing it”). The agenda for Skype sessions usually involves: review of the week and how the participant feels, checking the homework assigned in previous sessions, discussing the last module, demonstrating a certain exercise or practicing together with the participant and, at the end, planning homework that should be carried out until the next session.

For example, in the first and the second session the psychotherapist works with the patient to develop a case conceptualization in order to understand the origin of the problem and the mechanisms by which it is maintained. They then discuss the treatment plan so that the patient understands how the intervention will answer his/her needs. In the session following the third module, the psychotherapist briefly explains the hyperventilation process, describes and demonstrates the breathing control technique to the patient and then they practice it once together. In the end, the psychotherapist helps the patient find a time and place to practice the technique twice a day. After the interoceptive exposure module, the psychotherapist explains the rationale of the technique once more, encourages the patient and does a few exercises from the list together with the patient (e.g. breathing for 2 min through a straw, spin in a chair for 20–30 s, cover the head with a scarf or a jacket etc.).

The modules and the entire therapeutic environment of PAXonline are carefully designed in order to facilitate the psychotherapeutic process (e.g. personalization of intervention, organizing information and knowledge in learning objects and use of other effective chunking strategies, enhancing learnability by using multimedia content, use of three layers of information, providing immediate feedback to queries, teach-back exercises, providing a reward after each module completion, offering access to a personal portfolio and a virtual library etc.) [10, 85, 86]. The program also contains certain techniques aimed at improving adherence and compliance with the treatment, e.g. rewards after module completion (short movies that induce positive emotions), the “meditation of the day”, which is sent via e-mail every 5 days and contains a link to a short movie or animation that is meant to be inspirational and/ or motivational. The participants’ adherence is carefully monitored by measuring overall usage time, the modules and homework assignments completed, the time spent on each module and each module component.

#### Therapists

Three licensed psychotherapists with formal training in cognitive-behavioral therapy and a minimum of 3 years of clinical experience work with the participants allocated in the first treatment group. They have also participated in a 3 months blended course (3 face to face meetings plus online learning) prior to this study and were instructed in using the PAXonline platform and delivering CBT interventions online. The guidance will be delivered according to a standard treatment protocol, but it will also be personalized according to each participant’s need. During the study, the team meets once a month for discussions and the main researcher is available for contact at any time.

### Instruments

The selected instruments have already been well validated and are frequently used in CBT clinical trials for panic disorder in particular, as well as for other anxiety and mood disorders. Measures are taken at baseline (pre-treatment), 6 weeks after the intervention started (mid-treatment), directly after the intervention (post-treatment, 12 weeks after baseline), 1, 3, 6 and 12 months after the intervention ends. All self report measures are administered through the internet (secured links are used and all the data are encrypted) and the diagnostic interviews are conducted through secured Skype or by phone. The questionnaires, which were not yet validated for Romanian population, were previously translated in Romanian and underwent a rigorous back-translation process to ensure a good adaptation.

### Primary outcomes

The primary outcomes are the diagnostic status of the participants at post-assessment and symptoms of panic disorder as assessed with the PDSS-SR.

Panic Disorder Severity Scale – Self Report (PDSS-SR). PDSS is originally a face-to-face interview and was adapted to a self-report questionnaire by Houck et al. [87]. The scale contains seven items that measure the severity of seven dimensions of panic disorder and associated symptoms: 1) frequency of panic attacks; 2) distress during panic attacks; 3) anticipatory anxiety (worry about future panic attacks); 4) agoraphobic fear and avoidance; 5) interoceptive fear and avoidance (i.e., apprehension and avoidance of bodily sensations); 6) impairment of or interference with work functioning; and 7) impairment of or interference with social functioning. The PDSS-SR generates a total score ranging from 0 to 28, with a higher score indicating more severe panic symptoms. The questionnaire has good psychometric properties (Cronbach’s alpha = 0.92, test-retest reliability is 0.83) and is sensitive to changes following treatment [87]. A cut-off score of six may discriminate between the presence and absence of current DSM-IV panic disorder and a cut-off score of fourteen may discriminate between mild and severe panic disorder [82].

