### Objectives and research questions

The aim of the present trial is to investigate the clinical efficacy of an internet-based self-help treatment program for panic disorder with therapist guidance via secured Skype in Romanian adults. The program (PAXonline for panic disorder) has been developed de novo by the authors, based on empirically validated cognitive-behavioral models of anxiety disorders [74–76], and it is currently the only available psychological treatment of this kind in Romania. A secondary objective is to compare the guided self-help intervention to a similar but unguided intervention program, considering clinical outcomes, adherence to treatment and drop-out. Additional exploratory research will be conducted to identify potential predictors, moderators and mediators of treatment outcome, such as patients’ expectations, patient-therapist working alliance, panic disorders severity and comorbidity status, and other relevant factors that were chosen based on previous research findings.

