### Sample size

The effect sizes reported between guided and unguided interventions are quite heterogeneous with small to medium Cohen’s d size effects between 0.27 [64] and .42 [14]. Taking into consideration that, in most part, the guidance in previous studies was in fact low-intensity guidance, and that more support from a therapist yields larger effects [21, 62, 63], we expect an effect size of 0.5 (Cohen’s d) between guided and unguided treatment for PD. Based on this effect size, a power of 0.80, and an alpha level of 0.05, we would need 51 subjects in each condition. This recommended sample size has been increased to accommodate an attrition rate of 20 %. Thus, the study aims to achieve a sample of 192 participants.

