## Discussion

The prevalence of mental health problems is very high and bears considerable suffering and burden worldwide. However, only a small percentage of the affected individuals reach out and receive treatment for their problems. There are many barriers at different levels, yet a viable solution to increase access to quality treatment resides in the possibilities provided by internet-based cognitive behavioral treatments. Although several ICBT programs have been tested with strong positive results and even integrated into regular health care, there are countries where validated internet-based interventions are yet to be developed. The present trial aims both to validate the overall efficacy of the first Romanian ICBT program for panic disorder, and to investigate aspects that are novel to ICBT, such as brief therapist guidance sessions via secured Skype.

There are still divergent results regarding the effect of therapist guidance in ICBT [18, 31, 56–58], and the efficacy of Skype-based (or equivalent) therapy sessions in ICBT have not been previously investigated. Thus, a central focus of our trial is to test the additive effect of therapeutic guidance via secured Skype in self-help ICBT programs. Specifically, the current study design allows us to assess the effect of the same self-help intervention modules in two treatment conditions: therapist guided via Skype vs. unguided self-directed intervention.

There is a general consensus that internet-based therapy can be efficient for many psychiatric conditions, but not all the patients benefit from it [44]. Thus, there is an increasing interest to describe the characteristics of the patients who would benefit the most from this type of interventions. Taking into consideration this issue, additional exploratory analyses of potential predictors, moderators or mediators will be made. Patients’ treatment expectations, personality traits (e.g. personal autonomy), and usability of the online treatment program could prove to be key factors of treatment adherence and outcome, especially in the unguided self-help treatment group.

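### The primary claim is not fixed: two unranked primary outcomes, inconsistent primary time points and registry set, and a sample size built on a contrast labelled secondary; unadjusted pairwise testing would give a familywise error well above 5%

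*Protocol article*

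**What the plan says.** **Outcomes.** The Primary outcomes section says "The primary outcomes are the diagnostic status of the participants at post-assessment and symptoms of panic disorder as assessed with the PDSS-SR". It gives no ranking, no rule on whether one or both must succeed, and no time point for the PDSS-SR.

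**Time points.** The abstract puts the primary outcomes at 12 weeks and at follow-up months 3 and 6. Table 2 schedules the clinician interview only pre-intervention and at 12 weeks, and the Diagnostic interview section agrees. The PDSQ self-report scale is repeated at months 6 and 12, but it is the screening questionnaire, not the blinded interview, and it is not given at month 3.

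**Registry table (Table 1).** The primary outcomes are PDSS-SR, ACQ and BSQ. Diagnostic status is not among them. Table 2 lists ACQ and BSQ as secondary.

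**Contrasts.** Objectives and research questions makes the efficacy of the guided program the aim and adds: "A secondary objective is to compare the guided self-help intervention to a similar but unguided intervention program". The Sample size section is nevertheless built on that contrast: "we expect an effect size of 0.5 (Cohen’s d) between guided and unguided treatment for PD", followed by "Based on this effect size, a power of 0.80, and an alpha level of 0.05, we would need 51 subjects in each condition". The Discussion says "a central focus of our trial is to test the additive effect of therapeutic guidance via secured Skype in self-help ICBT programs".

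**Analysis.** Statistical analysis names a linear mixed model and chi-square tests. It does not say which contrast or time point leads, or whether the three arms are compared jointly or in pairs.

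**The concern.** Several results could each be presented as the positive primary finding. At week 12 there are two outcomes and three pairwise contrasts, so six tests. The waiting list is not available at follow-up (Discussion), so months 3 and 6 add only guided versus unguided. That makes two more tests on the PDSS-SR, eight in all.

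The only significance level stated is an undivided 0.05 for one contrast. With the lead outcome, visit and contrast left open or contradictory, the main result could be chosen after the data are seen, and the error rate of a primary claim would no longer be the 5% a reader expects. Which endpoint and contrast lead is core protocol content. A later analysis plan could add a multiplicity method, but the conflicts between sections would remain in this text.

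**Working it through.** **1. The plan's own figure.** Inputs from the Sample size section: d = 0.5, power 0.80, alpha 0.05, attrition 20%.
- Formula: n per arm = 2(z_alpha + z_beta)² / d².
- One-sided 0.05: 2(1.645 + 0.842)² / 0.25 = 49.5, so 50. The t-based calculation gives 50.15, so 51. This matches.
- Two-sided 0.05: 2(1.960 + 0.842)² / 0.25 = 62.8, so 63 (t-based 63.77, so 64). This does not match.
- Attrition: 51 / 0.80 = 63.75, so 64; 3 × 64 = 192. This matches.

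The whole 0.05 is therefore spent on guided versus unguided, and 51 is reproduced only with a one-sided test.

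**2. Error rate if nothing is adjusted.** Normal test statistics were simulated (400,000 to 1,000,000 runs per setting) for three equal arms that share data across contrasts. A false claim is any |z| > 1.96. The correlations are assumptions, because the protocol gives none: 0.3-0.7 between the two outcomes and 0.5-0.7 between visits.

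| Family of tests | True state | Chance of at least one false claim |
|---|---|---|
| PDSS-SR, 3 contrasts, week 12 | no differences | about 12% |
| Both outcomes, 3 contrasts, week 12 | no differences | 20-22% |
| The same plus guided vs unguided PDSS-SR at months 3 and 6 | no differences | 24-28% |
| Guided vs unguided, both outcomes, week 12 | both programs beat waiting list equally | 8-10% |
| The same plus PDSS-SR at months 3 and 6 | as above | 14-17% |
| One three-arm test per outcome, week 12 | no differences | 8.4-9.5% |

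Treating the six week-12 tests as independent would give 1 − 0.95⁶ = 26.5%, which is too high because they share arms and participants. Widening the between-outcome correlation to 0-0.9 gives 17-23% at week 12 and 21-29% with the two follow-up tests.

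**3. The proposed procedure.** With three arms, a 2-df test at 0.05 followed, only if significant, by the three pairwise tests at 0.05 is a closed procedure. Simulated familywise error for the PDSS-SR under the global null: 5.0-5.1%.

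**4. The alternative of splitting alpha.** With 51 per arm and d = 0.5, two-sided t-test power is about 71% at 0.05 and 54% at 0.05 / 3 = 0.0167. The fair comparison is 71% with 54%. The gap between 80% and 71% comes from the one-sided sample-size calculation, which is a separate matter.

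**The case against.** **A reader might infer that the protocol tests every outcome, contrast and visit at 0.05 with no order at all, so that a false-claim rate of 20-28% is a property of the plan.** The document does not support this. Alpha appears once, in the sample-size sentence, and no section sets a per-test level or announces separate pairwise tests. A multiplicity rule may sit in a fuller protocol or analysis plan that is not shown, and its absence from an article is not a fault. The one-factor design fits a joint three-arm test equally well. The objectives do rank the contrasts, so the lack of order applies to the outcomes and visits only. If both outcomes had to succeed for a contrast, the error for that contrast would be at or below 5%. The global null is also demanding: if both programs work, only guided versus unguided can produce a false claim.

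It can further be said that sizing a trial on its smallest expected effect does not make that contrast primary, and that a phrase in the Discussion is not a design statement.

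All of this stands against an unconditional error rate. It does not remove the textual conflicts. The abstract, Table 1, Table 2 and the Primary outcomes section do not agree on what is primary or when. No success rule links the two outcomes. The ranking of contrasts in the objectives is not carried into the sample size or analysis. Even one three-arm test per outcome would exceed 5% if either outcome sufficed.

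**Conclusion.** The concern holds as a badly fixed primary claim, not as a demonstrated 20-28% error rate. What the text itself shows is two unranked primary outcomes, follow-up visits that the abstract makes primary but the interview schedule cannot supply for diagnostic status, a different primary set in the registry table, and a trial sized on a contrast its objectives call secondary.

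The size is conditional on unadjusted two-sided pairwise tests, either outcome sufficing, and the assumed correlations: about 20-22% at week 12 and 24-28% with the two follow-up tests when no arm differs. The more realistic figures are those for guided versus unguided when both programs work: about 8-10%, rising to 14-17% with follow-ups, which is roughly two to three times 5%. The simulation uses simple test statistics in place of the mixed model, so it shows scale and is not a prediction for the planned analysis.

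**What to change.** Issue a dated, justified amendment before outcome data are examined:
- Name PDSS-SR at week 12 as the single primary endpoint.
- Test the 2-df three-arm effect at 0.05. Only if it is significant, test the three pairwise contrasts at 0.05 each.
- Make diagnostic status at week 12 the key secondary, and test a contrast on it only if the same contrast succeeded on the PDSS-SR. Claim strong control across both outcomes only if diagnostic status is tested, by the same two steps, after all three PDSS-SR contrasts have succeeded.
- Treat months 3 and 6 as secondary.
- Reconcile the abstract, Objectives, Table 1, Table 2, Primary outcomes and Sample size on the primary set and the lead contrast, and update the registry to match.

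Requiring both outcomes to succeed for the same contrast would be another valid rule for the two outcomes, but it costs power, and the contrasts and visits would still need an order.

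**Cost.** No new data and little loss of power on the PDSS-SR, compared with the fall from 71% to 54% under a three-way Bonferroni split. Diagnostic status would no longer support a stand-alone primary claim. Because 99 participants had been recruited by December 2015 and participants and therapists are unblinded, the amendment must record its date, its reason and the fact that outcome data had not been examined.
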